# CATCH: a randomised clinical trial comparing long-term tinzaparin versus warfarin for treatment of acute venous thromboembolism in cancer patients

**DOI:** 10.1186/1471-2407-13-284

**Published:** 2013-06-13

**Keywords:** Venous thromboembolism, Cancer, LMWH, Tinzaparin, Warfarin, CATCH, Recurrent, Symptomatic, Incidental, Health-related quality of life

## Abstract

**Background:**

Low-molecular-weight heparin (LMWH) is recommended and commonly used for extended treatment of cancer-associated thrombosis (CAT), but its superiority over warfarin has been demonstrated in only one randomised study. We report here the rationale, design and *a priori* analysis plans of Comparison of Acute Treatments in Cancer Haemostasis (CATCH; NCT01130025), a multinational, Phase III, open-label, randomised controlled trial comparing tinzaparin with warfarin for extended treatment of CAT.

**Methods/Design:**

The primary objective is to assess the efficacy of tinzaparin in preventing recurrent venous thromboembolism (VTE) in patients with active cancer and acute, symptomatic proximal deep vein thrombosis and/or pulmonary embolism. The secondary objectives are to determine: safety of tinzaparin given over 6 months; clinical and laboratory markers for recurrent VTE and/or major bleeding; 6-month overall mortality; incidence and severity of post-thrombotic syndrome; patient-reported quality of life; and healthcare resource utilisation. Nine hundred patients are randomised to receive tinzaparin 175 IU/kg once daily for 6 months or initial tinzaparin 175 IU/kg once daily for 5–10 days and dose-adjusted warfarin (target INR 2.0–3.0) for 6 months. The primary composite outcome is time to recurrent VTE, including incidental VTE and fatal pulmonary embolism. All patients are followed up to 6 months or death, whichever comes sooner. Blinded adjudication will be performed for all reported VTE, bleeding events and causes of death. Efficacy will be analysed using centrally adjudicated results of all patients according to intention-to-treat analysis. An independent Data Safety Monitoring Board is reviewing data at regular intervals and an interim analysis is planned after 450 patients have completed the study.

**Discussion:**

The results will add significantly to the knowledge of the efficacy, safety and cost effectiveness of tinzaparin in the prevention of recurrent VTE in patients with cancer and thrombosis. Prospective data will emerge on the clinical significance of incidental VTE and risk stratification in patients with CAT. Results on post-thrombotic syndrome, quality of life and healthcare resource utilisation will inform decision makers on how to secure better patient care. If tinzaparin is shown to be more effective than warfarin, CATCH will provide valuable confirmatory data to support the use of the LMWH tinzaparin for extended treatment of CAT.

## Background

### Cancer and venous thromboembolism

Cancer patients are known to be at higher risk of developing venous thromboembolism (VTE) compared with the general population [1-3]. VTE is a major cause of morbidity and mortality and is the second most common cause of death in patients with cancer [4,5]. Moreover, with the increasing incidence and prevalence of cancer, combined with more aggressive, often thrombogenic treatment regimens and surgery, the prevalence of cancer-associated thrombosis can be expected to increase.

The incidence of symptomatic VTE in cancer patients varies widely, with reported rates of 2% to 30%. This variation is likely to reflect not only the natural history of different tumour types [6-8] but also the influence of tumour-related factors (e.g. tumour location, presence of distant metastases) [1,7,9,10], treatment-related factors (e.g. surgery, chemotherapy) [11,12] and patient-related factors (e.g. older age, co-morbidities, multiple surgeries) [9]. The true rate of VTE is probably even higher than reported rates as many cases remain undetected. As part of an increasing focus on staging procedures, treatment modalities, treatment outcomes and improving cancer survival, the significance of asymptomatic or incidental events is becoming increasingly recognised [13]. Indeed, during the past decade, computed tomography (CT) scans have been used with greater frequency for the routine assessment of cancer staging and disease monitoring and, concordant with this, there has been increased reporting of incidental VTE, especially pulmonary embolism (PE), in cancer patients [14]. Neither the prognostic impact nor the treatment of incidental PEs in cancer patients is completely understood, but the consensus is that these events should be treated [15]. This is supported by data showing that the prevalence of incidental PE is clinically relevant and potentially associated with an unfavourable outcome [16,17].

### Treatment of VTE in cancer patients

Guidelines in Europe and North America recommend long-term treatment of symptomatic VTE in all cancer patients [18,19]. Major treatment objectives are to diminish the acute symptoms of deep vein thrombosis (DVT) and/or PE, reduce recurrent thrombosis, and reduce both fatal and non-fatal PE. Treatment of VTE should also reduce the incidence of long-term sequelae, such as post-thrombotic syndrome (PTS). With improved oncology treatment options leading to longer life expectancy, the benefits of long-term treatment of VTE are becoming increasingly relevant to patients with cancer. This trend towards better care might be expected to have a positive impact on a patient’s quality of life (QoL); however, relatively little is known about this important topic and further investigation of patient-reported outcomes is warranted.

For the general population, the standard treatment for acute VTE consists of initial therapy with a low-molecular-weight heparin (LMWH) followed by longer-term treatment (3–6 months) with an oral vitamin K antagonist (VKA). Although this approach can be effective for many patients, cancer patients have a substantial risk of recurrent VTE. Several studies have reported incidences of recurrent VTE as high as 20% in patients with cancer [20,21]. However, studies on how to treat and identify those at risk of recurrent VTE are limited [22,23]. Moreover, the frequent monitoring and dose adjustments required for VKA treatment have a negative impact on QoL [24]. Oral anticoagulant therapy with VKAs or novel oral anticoagulants, e.g. dabigatran and rivaroxaban, may also be problematic in patients with cancer because of drug interactions, malnutrition, vomiting and mucositis, and renal and liver dysfunction, all of which can lead to unpredictable bioavailability and variable levels of anticoagulation. Patients with advanced cancer may also have problems swallowing oral medications. Furthermore, the efficacy and safety of novel oral anticoagulants have yet to be determined in cancer patients and there is no antidote to reverse the anticoagulant effect of these drugs in cases of severe bleeding or when acute surgical intervention is necessary.

Unlike VKAs, LMWHs have predictable pharmacokinetic profiles and very few drug interactions [25]. LMWHs have been shown to have clinical benefit over VKAs in the secondary prevention of VTE in cancer patients [26-29]. Consequently, major consensus evidence-based guidelines on anticoagulation recommend that LMWHs be used for 3–6 months for the treatment of acute VTE in patients with active cancer (ASCO [30], ESMO [31], NCCN [32] and ACCP [15]). Although only the CLOT study has demonstrated statistically significant reduction in symptomatic VTE using dalteparin compared with VKA [28] (Table 1), all three major LMWHs (dalteparin, enoxaparin and tinzaparin) are recommended in guidelines. In the CLOT trial, dalteparin was given at a full, therapeutic dose for the first month followed by 75–80% of the full dose from month 2 to 6. In contrast, full doses of LMWH were given throughout the entire treatment period in the CANTHANOX, ONCENOX and LITE studies (Table 1). Whether this latter approach would have resulted in lower risks of VTE recurrence or higher risks of bleeding in CLOT is unknown. None of these previous trials addressed questions regarding PTS, QoL, predictors of recurrence, and the cost effectiveness of LMWH monotherapy, all of which are important considerations for long-term therapy in a complex patient population with reduced life expectancy. Finally, the open-label design of published trials and the perceived patient preference of oral therapy over subcutaneous injections led the ACCP to downgrade its previous 1A recommendation from the 2008 guidelines to 2B in its most recent review [15]. In addition, the lack of confirmatory studies may explain the continued widespread use of VKAs [33,34]. To narrow these gaps in knowledge, and to provide additional data to support multiple guidelines that recommend prolonged treatment with LMWH as the preferred anticoagulant for cancer-associated thrombosis, we are conducting CATCH (Comparison of Acute Treatments in Cancer Haemostasis), a multinational, open-label, randomised controlled trial designed to compare tinzaparin (innohep®, LEO Pharma A/S) with warfarin for the extended treatment of cancer-associated VTE.

**Table 1 T1:** **Randomised clinical trials of VTE treatment in patients with cancer (adapted from Khorana 2009**[18]**)**

**Study**	**n**	**Population**	**Treatments**	**Follow-up**	**Outcomes**	**Key limitations compared with the CATCH study design**
CLOT [28]	672	Acute symptomatic proximal DVT and/or PE	Dalteparin qd (5–7 days) + warfarin* (6 months)	6 months	**Recurrent VTE (primary)** 15.8% (W), 8.0% (D); *P* = 0.002	Full-dose dalteparin not maintained for entire 6-month treatment period
			Dalteparin qd (6 months)^†^		**Major bleeding** 4% (W), 6.0% (D); *P* = 0.27	No outcomes for PTS, HRQoL, predictors of recurrence, and healthcare resource utilisation
Main-LITE^‡^[27]	200	Proximal DVT	UFH + warfarin (6 days) then warfarin (3 months)	3 months and 12 months	**Recurrent VTE (primary)** 3 months: 10.0% (W), 6.0% (T) 12 months: 16.0% (W), 7.0% (T); *P* = 0.044	Duration of randomised treatment only 3 months
			Tinzaparin qd (3 months)		**Major bleeding** 3 months: 7.0% (W), 7.0% (T)	Modest sample size with limited statistical power
CANTHANOX [29]	146	DVT and/or PE	Enoxaparin qd (initial) + warfarin (3 months)	3 months	**Treatment failure**^**§ **^**(primary)** 21.1% (W), 10.5% (E); *P* = 0.09	Composite primary endpoint (recurrent VTE and major bleeding)
			Enoxaparin qd (3 months)		**Major bleeding** 16.0% (W), 7.0% (E); *P* = 0.09	Duration of randomised treatment only 3 months Small study with limited statistical power Trial stopped early because of slow recruitment
ONCENOX [26]	122	Acute symptomatic VTE	Enoxaparin LD bid (5 days) + warfarin (6 months)	6 months	**Recurrent VTE (secondary)** 10.0% (W), 6.9% (LD), 6.3% (HD)	Recurrent VTE was only a secondary objective (study did not meet its primary objective, which was to recruit the necessary number of patients within a 12-month time frame) Small study with limited statistical power
			Enoxaparin LD bid (5 days) then LD qd (6 months)			
			Enoxaparin LD bid (5 days) then HD qd (6 months)		**Major bleeding** 2.9% (W), 6.5% (LD), 11.1% (HD)	

*Except in Spain and The Netherlands, where acenocoumarol was used; ^†^full dose (200 IU/kg) for first month then reduced dose (~150 IU/kg) for the remaining 5 months; ^‡^cancer subpopulation; ^§^composite endpoint of recurrent VTE and/or major bleeding within 3-month treatment period.

Abbreviations: *bid* twice daily; *D* dalteparin, *DVT* deep vein thrombosis, *E* enoxaparin, *HD* high dose (1.5 mg/kg), *HRQoL* health-related quality of life, *LD* low dose (1.0 mg/kg), *PE* pulmonary embolism, *PTS* post-thrombotic syndrome, *qd* each day, *T* tinzaparin, *UFH* unfractionated heparin, *VTE* venous thromboembolism, *W* warfarin.

### Main study objectives

The main aim of CATCH is to compare the efficacy of tinzaparin with warfarin in preventing the recurrence of VTE in patients with active cancer. Secondary objectives are: to assess the safety of long-term tinzaparin; to identify clinical risk factors for recurrent VTE and bleeding; to assess overall mortality at 6 months; to identify the possible role of coagulation parameters in predicting recurrent thrombosis or prognosis; to assess the incidence and severity of PTS; to assess patient-reported QoL; and to assess healthcare resource use for the treatment of cancer-associated VTE.

## Methods

### Study design

CATCH is a Phase III, multinational, concealed, randomised, active-controlled, open-label trial with blinded adjudication assessing the efficacy and safety of long-term (6 months) tinzaparin therapy versus anticoagulation with warfarin for the treatment of VTE in cancer patients (Figure 1). It is being conducted in more than 160 sites across five continents.

**Figure 1 F1:**
[figure not shown]
Study design, interventions and timelines.

### Study population

Adult patients (≥18 years or above legal age of consent) with a diagnosis of active cancer and a histologically or cytologically confirmed solid tumour (evidence of early-stage, regionally advanced or metastatic disease) or haematological malignancy are eligible for inclusion. Active cancer is defined by any of the following: diagnosis of cancer within the past 6 months; recurrent, regionally advanced or metastatic disease; any treatment for cancer during the previous 6 months; not in complete remission of a haematological malignancy. Participants must also have symptomatic and objectively confirmed acute proximal DVT and/or PE (Table 2). Other inclusion criteria include Eastern Cooperative Oncology Group (ECOG) performance status of 0, 1, or 2 prior to VTE.

**Table 2 T2:** Diagnostic criteria for VTE

	**VTE before randomisation**	**Recurrent VTE after randomisation**
Symptomatic VTE	• All patients must have diagnostic imaging performed of both legs and the lungs in order to determine baseline presence or absence of DVT or PE.	• Standard objective imaging is required to diagnose recurrent VTE. If there are symptoms from the leg(s) AND lungs, objective imaging is required for both sites.
	• Diagnostic imaging results for DVT:	• Diagnostic imaging results for recurrent DVT:
	- A non-compressible venous segment of the proximal deep veins in the legs, including iliac, femoral and popliteal veins.	- A non-compressible venous segment of the deep veins (proximal and/or distal) in the legs that had normal compression at baseline.
	- An intraluminal filling defect on venography, CT scan or MR venography of the proximal deep veins in the leg.	- A new or extension of 5 cm or greater of intraluminal filling defect on venography, CT scan or MR venography of the deep veins in the leg, including inferior vena cava.
	• Diagnostic imaging results for PE:	- An extension of non-visualisation of the deep veins of the leg in the presence of a sudden cut-off on venography, CT scan or MR venography.
	- An intraluminal filling defect on CT pulmonary angiography.	• Diagnostic imaging results for recurrent PE:
	- A perfusion defect of at least 75% of a segment with a local normal ventilation result (mismatch defect) on ventilation-perfusion lung scintigraphy (high-probability scan).	- A new or extension of an existing intraluminal filling defect on CT pulmonary angiography.
	- A non-high, non-diagnostic ventilation-perfusion lung scan with confirmed DVT.	- A new sudden cut-off of vessels more than 2.5 mm in diameter on CT pulmonary angiography.
		- A new perfusion defect of at least 75% of a segment with a local normal ventilation result (mismatch defect) on ventilation-perfusion lung scintigraphy (high-probability scan).
		- A non-high, non-diagnostic ventilation-perfusion lung scan with confirmed DVT.
		• Diagnostic criteria for fatal PE:
		- Objective testing as above associated with death.
		- Autopsy finding of PE contributing to death.
		- Sudden and unexplained death within the 6-month study period which cannot be attributed to a documented cause and for which PE is the most probable cause.
Incidental VTE	• Not valid as an inclusion criterion.	• Incidental PE or DVT are defined as thrombi that were reported during imaging testing performed for reasons other than for suspected PE or DVT.
	• Diagnosis of incidental VTE during the required baseline imaging represents the baseline status.	• The same diagnostic imaging criteria for recurrent DVT or PE apply to confirming the presence of an incidental DVT or PE.
		• Incidental DVT is only included as an outcome if located in the popliteal or more proximal leg veins.
		• Incidental PE is only included as an outcome if located in segmental or more proximal pulmonary arteries.
		• In patients with incidental PE involving subsegmental pulmonary arteries only, a compression ultrasound showing a new DVT is necessary to confirm a recurrent thrombotic event.

Exclusion criteria include the following: life expectancy <6 months; basal cell carcinoma or non-melanoma skin cancer (in the absence of any other cancer diagnosis); creatinine clearance ≤20 mL/min (according to the abbreviated Modification of Diet in Renal Diseases formula); contraindications to anticoagulation; known hypersensitivity to study medications; history of heparin-induced thrombocytopenia (HIT); therapeutic anticoagulation for >72 hours pre-randomisation; receiving therapeutic anticoagulation at the time of VTE; unlikely to comply with protocol; participation in another interventional study; women of childbearing potential or fertile men not using effective contraception.

The eligibility criteria are very similar to those of previous trials to facilitate cross-trial comparison and possible meta-analysis of the results.

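### Table 2 counts a non-diagnostic lung scan plus a DVT as recurrent PE without requiring the DVT to be new or extended

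*Protocol article*

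**What the plan says.** Table 2 of the protocol article (Methods, Study population) has one column for VTE before randomisation and one for recurrent VTE after it. The last imaging criterion for recurrent PE is "A non-high, non-diagnostic ventilation-perfusion lung scan with confirmed DVT". The baseline column carries the same line, word for word.

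The lines around it in the recurrence column are worded differently. For PE on CT they read "A new or extension of an existing intraluminal filling defect on CT pulmonary angiography" and "A new sudden cut-off of vessels more than 2.5 mm in diameter on CT pulmonary angiography". For DVT on ultrasound, the non-compressible segment must be one "in the legs that had normal compression at baseline". For an incidental PE confined to subsegmental arteries, "a compression ultrasound showing a new DVT is necessary to confirm a recurrent thrombotic event".

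The first fatal-PE criterion is "Objective testing as above associated with death", so it takes over whatever the imaging list allows.

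The section on primary and secondary efficacy outcomes makes Table 2 the standard for endpoint events and admits to the primary analysis only those the independent committee has confirmed. Baseline imaging is mandatory: "All patients must have diagnostic imaging performed of both legs and the lungs in order to determine baseline presence or absence of DVT or PE".

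**The concern.** Patients qualify with proximal DVT, PE or both, so some start the trial with a confirmed DVT. If that DVT is still visible when the patient later has chest symptoms and an inconclusive lung scan, the criterion is met as written although neither test has shown anything new. The event would enter the primary composite and the symptomatic-PE component or, if the patient died, fatal PE.

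Events of this kind that arise equally in both arms pull the comparison towards no difference and cost power. The planned blinded sample size re-estimation would not reveal this. It keeps the 50% reduction fixed, and false events raise the pooled rate, so the design would look better supplied with events while the true contrast shrank.

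**Working it through.** **1. The criteria side by side** (Table 2, recurrence column)

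| Criterion | Is change from baseline required? |
|---|---|
| DVT, compression ultrasound | Yes: segment compressed normally at baseline |
| DVT, filling defect | Yes: new, or extended by at least 5 cm |
| DVT, non-visualisation | Yes: extension |
| PE, CT filling defect | Yes: new or extended |
| PE, CT vessel cut-off | Yes: new |
| PE, high-probability lung scan | Yes: new perfusion defect |
| PE, non-diagnostic scan with DVT | **No** |
| Incidental subsegmental PE | Yes: new DVT on ultrasound |

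One line of eight lacks the requirement, and it is the one carried over unaltered from the baseline column.

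**2. Two patients traced through the rule**

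- *Patient A* has a persisting index DVT, new chest symptoms and a non-diagnostic scan. No recurrent-DVT criterion is met and no other PE criterion is met. The line at issue is met, so the patient is a primary-endpoint event with no new thrombus shown.
- *Patient B* has chest symptoms only, a non-diagnostic scan and a new DVT in a leg without symptoms. This is not plainly a symptomatic DVT. It is not incidental either, because the imaging was done for suspected VTE. The line at issue captures this patient, properly, as symptomatic PE.

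The line therefore admits both a genuine recurrence and a possible non-event.

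**3. The plan's sample size, reproduced**

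Inputs (Sample size estimation): control rate 12.6%, relative reduction 50% (so 6.3% on tinzaparin), two-sided alpha 0.05, power 90%, 1:1 allocation.

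- Hazard ratio: ln(1 − 0.063) / ln(1 − 0.126) = 0.483.
- Events (Schoenfeld): 4 × (1.960 + 1.282)² / (ln 0.483)² = 79.4, rounded up to 80.
- Patients: 80 / [(0.126 + 0.063)/2] = 80 / 0.0945 = 847, the stated figure.

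**4. Illustration of the possible cost**

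The article does not say how often the line would be used. *Assumption:* a fraction f of otherwise event-free patients become false events, equally in both arms. Each rate p becomes p + f(1 − p). With D = 847 × the mean rate, power is Φ(√D × |ln HR| / 2 − 1.960).

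| f | Control | Tinzaparin | Risk ratio | HR | Events D | Power |
|---|---|---|---|---|---|---|
| 0 | 12.60% | 6.30% | 0.50 | 0.483 | 80.0 | 90.2% |
| 0.5% | 13.04% | 6.77% | 0.52 | 0.502 | 83.9 | 88.5% |
| 1% | 13.47% | 7.24% | 0.54 | 0.519 | 87.7 | 86.7% |
| 2% | 14.35% | 8.17% | 0.57 | 0.551 | 95.4 | 83.0% |
| 3% | 15.22% | 9.11% | 0.60 | 0.579 | 103.1 | 79.3% |

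A second calculation adds 1 or 2 percentage points to each arm:

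- 13.6% against 7.3% gives a reduction of 1 − 7.3/13.6 = 46%.
- 14.6% against 8.3% gives a reduction of 1 − 8.3/14.6 = 43%.
- A simulated log-rank test (900 patients, 5% dropout, competing deaths not modelled, 8,000 runs) gave power of 90.2% with no false events, 87.4% with 1 point and 83.6% with 2 points.

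The two methods agree within one percentage point.

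For scale, the planned rates imply 450 × 0.126 + 450 × 0.063 = 56.7 + 28.35, about 85 true events. The 1% case adds about 9 (11%) and the 2% case about 18 (21%).

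**The case against.** The best defence is context. The line sits in a column for recurrent events, under a heading for recurrent PE and straight after DVT criteria that all demand change, so a DVT confirmed after randomisation can be read as one that meets those criteria. Events count only once a blinded expert committee confirms them, and its charter, which is not shown, may require a new DVT. This stands as a reason to expect fewer false events than the wording permits. It does not cure the wording: the neighbouring lines share the same heading and still spell out the requirement, and the committee's standard is Table 2 itself. Blinding prevents a classification that favours one arm, but it does not correct a criterion that is too wide.

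The frequency may also be low. A false event needs new symptoms, a lung scan rather than CT angiography, an inconclusive result, a persisting index DVT and acceptance by the committee. The 2% case would mean about a fifth more events from one fallback criterion. That stands too, which is why the power figures are only an illustration.

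Two stronger readings are tempting. A reader might infer that the line adds *only* patients with an old DVT, since a new one already counts as recurrent DVT. Patient B shows otherwise. A reader might also infer that, in an open-label trial, lung scans would be ordered more often in one arm. The article gives no evidence of this: under Study follow-up, both arms have the same standardised symptom assessment and the same objective testing for suspected recurrence.

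**Conclusion.** The criterion is wrong as written. It is the only recurrent-VTE imaging criterion in Table 2 that can be met without any change from baseline, and it feeds the primary endpoint and, by reference, fatal PE.

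The size of the effect is unknown and may be small. The loss of 3 to 7 percentage points of power at 1% to 2% false events rests wholly on an assumed rate, equal in both arms. Under that assumption the error dilutes a true effect and does not manufacture superiority.

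A reader might go further and infer that false events have already been counted, or that the primary result is at serious risk. The article supports neither: it reports no adjudicated events and gives no data on lung-scan use. This is a moderate correction, worth making because it is cheap and concerns the primary endpoint.

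**What to change.** Keep the line, because it serves patients with chest symptoms and a new DVT in a symptom-free leg. In the recurrence column, end it with: *with a DVT that meets the recurrent-DVT criteria above, compared with baseline leg imaging*. The fatal-PE line then follows by reference. Put the same wording in the adjudication charter. Before unblinding, have the blinded committee check any event accepted on this line alone.

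The cost is one line in Table 2, a matching line in the charter and a short check. Leg imaging at baseline is already required of every patient, so no new data are needed. The stated sample size does not change. The downside is that a few events may be lost, for example where a DVT has extended by less than the 5 cm that the filling-defect criterion demands.
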